**Fig. 2 Fig2:**
[figure not shown]
OTIP risk classification

With the support of Kybele, the national trainers–GHS healthcare staff (OB-GYN doctors and midwives) who were part of the pilot OTIP program— train the champion midwives in their own hospital premises. The first day of training covers motivation on the job, clinical knowledge, as well as theoretical and practical session on how to use the new obstetric package (i.e., triage assessment forms, risk acuity charts and color-coded bands), and how to develop and implement care plans based on the diagnosis and risk status of patients.

The second day of training covers a module on monitoring (i.e., record keeping) and leading (i.e., how to deal with change opposition) OTIP’s implementation. The next two days consist of formal training sessions led by the Champions, where they teach their own peers the content of the first day of training with support and guidance from the national trainers. The final day consists of setting up the new triage area. After hospital management identifies an appropriate area, Champions help to clean, order, and arrange the necessary equipment (plus vital signs monitoring tools donated by Kybele), assessment surveys and forms, as well as color-coded bands. Champions also select among themselves who the triage in-charge will be.

The selection of Champions among midwives is conducted by either hospital management or fellow midwives. They are selected based on criteria that capture the extent to which midwives have leadership and teaching abilities. The exact content was developed from Kybele’s prior experience in Ghanaian hospitals.

#### Outcomes

We consider two sets of primary outcomes:Process variables: Representing the actual medical care received by mothers and their new-borns (e.g., time until initial assessment; assessment received upon arrival; doctor intervened if complications during labour and delivery at the hospital; postnatal checks).Maternal and neonatal outcome variables: Including the health of pregnant women and new-borns (e.g. maternal and neonatal mortality; complications during labour and delivery at the hospital; APGAR scores).

To examine mechanisms behind potential impacts of OTIP on the primary outcomes, we further consider secondary outcomes:Hospital staff outcomes: Such as improved knowledge and midwives’ attitudes capturing their perceptions of autonomy, empowerment and motivation.

#### Sample size and power

The cRCT will focus on 25 OTIP hospitals. We aim to interview on average 30 hospital staff per hospital and 50 mother-newborn pairs. In total, the sample for the cRCT will be 750 staff, and 1250 mother/newborns per data collection round.

We calculate minimum detectable effects (MDEs) using the following formula [13]:1$$MDE\left(\frac{\left(t_{\alpha/2}+t_\beta\right)^2\sigma^2(mp\left(1-R_c^2\right)+\left(1-p\right)\left(1-R_p^2\right)}n\right)^\frac12$$

$$\:\alpha\:$$ denotes the significance level, $$\:\beta\:$$ power, $$\:\rho\:$$ unconditional ICC, $$\:t$$ is the critical values of the t-distribution, $$\:\sigma\:$$ is the standard deviation of the outcome,$$\:\:n$$ is midwives/mothers per arm, $$\:m$$ is midwives/mothers per cluster, $$\:{R}_{c}^{2}$$ is proportion of cluster level variance component explained by covariates and $$\:{R}_{p}^{2}$$ is the individual equivalent. One can interpret the effect of $$\:{R}_{c}^{2}$$ and $$\:{R}_{p}^{2}$$ as altering the “variance inflation factor” of the power calculation– when they equal zero the formula reduces to the standard cRCT one, applicable in our case.

To calculate the minimum detectable effects (MDEs), we assume a significance level ($$\:\alpha\:$$) of 0.05 and power ($$\:\beta\:$$) of 0.8 using two-sided tests.

To estimate intra-cluster correlations (ICCs) for the outcomes we measure, we reference the 2005 WHO Global Survey on Maternal and Perinatal Health [14], which presents ICCs that were obtained from 97,095 pregnancies and 98,072 births taking place in a representative sample of 120 hospitals in eight Latin American countries:Process variables: ICCs range from a minimum of 0.0003 to a maximum of 0.563, with a median of 0.067.Maternal outcome variables: Median ICC of 0.011 (interquartile range 0.007–0.037).Neonatal outcomes: Median ICC of 0.054 (interquartile range 0.013–0.075).

For hospital staff outcomes, we use data collected by colleagues on midwives in Nigeria to get an idea of hospital staff outcomes. The data provide indices that capture emotional exhaustion, accomplishment, and depersonalization (based on the Maslach Burnout Inventory).Hospital staff outcomes: ICCs of 0.07 for emotional exhaustion, 0.12 for accomplishment, and 0.07 for depersonalization.

As we will collect baseline data, we will be able to gain precision, allowing us to reduce ICC. We therefore assume ICCs of between 0.01 and 0.3 for process outcomes, 0.01 for maternal and neonatal outcomes, and no more than 0.1 for hospital staff outcomes.

Table 1 provides MDEs for all outcome groups. We note that since we assume that all outcomes considered will be continuous normally distributed variables standardized to have mean zero and standard deviation of one relative to the control group, the estimated MDE’s do not vary by outcomes, but rather by sample size we have for each outcome group.

**Table 1 Tab1:** Minimum detectable effects (standard deviations)

Outcome	MDE for different ICCs		
	0.01	0.1	0.3
Process (1,250)	0.196	0.390	0.637
Mother/child (1,250)	0.196	0.390	
Midwife level (750)	0.236	0.410	

For process variables, our RCT sample yields MDEs between 0.196 and 0.64 for two-sided tests. For maternal and newborn outcomes, the MDE is between 0.196 and 0.39. For hospital staff outcomes, the expected MDE is between 0.36 and 0.41.

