#### Statistical methods

For our process variables, we will estimate the intent-to-treat effect of the program. Our design is a cluster randomized controlled trial stratified by region.

We estimate the impact of OTIP on process and maternal and neonatal outcomes by estimating the following specification for the outcome *Y* of mother or baby *i* in hospital *j* in region *r* at time *t*:2$$Y_{ij}=\beta\;OTIP_j+\delta\;X_{ij}+Y_r+\epsilon_{ij}$$.

Where $$\:OTI{P}_{j}$$ indicates if a hospital is allocated to receive OTIP early, $$\:{\varvec{X}}_{ij}$$ is a vector of controls for hospital characteristics selected by machine learning methods, and $$\:{\gamma\:}_{r}$$ are region fixed effects, as we stratified our randomisation by region to ensure balance in earlier and later treated hospitals in each region.

To increase statistical power, we will leverage the panel nature of our data and use baseline values of the outcomes in our analysis. For observations with values collected at baseline and follow-up, we can use an ANCOVA design. For observations without baseline values, we can use a difference-in-differences specification, exploiting variation across early- and later-treated hospitals, before and after the introduction of OTIP in early-treated.

To investigate mechanisms behind the observed impacts, we will use the same design with hospital staff outcomes to understand whether any impacts are driven by changes in staff outcomes due to OTIIP, such as midwives’ clinical knowledge and attitudes.

Moreover, for outcomes with low serial correlation, we will follow [15] and pool the multiple follow-up measurements to average out noise and increase power.

Due to the small number of clusters (25), we will present a wild-bootstrap p-value that is robust to small numbers of clusters [16]. We will additionally adjust for multiple hypothesis testing by family of outcome. Lastly, we will test for balance using baseline data for outcomes for hospital, midwives and patients’ characteristics. We will also test if attrition is uncorrelated to treatment allocation, and in case of non-random attrition on treatment status, we will estimate our main specification using inverse probability weighting.

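### The ICC of 0.01 assumed for neonatal outcomes lies below the lower quartile of the protocol's own source, so the 0.196 SD lower bound of the detectable-effect range is unsupported for them

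*Protocol article*

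**What the plan says.** All from the Protocol article.

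- **Sample size and power, source.** The ICCs come from a WHO survey of 120 hospitals in eight Latin American countries. For newborns: "Neonatal outcomes: Median ICC of 0.054", interquartile range 0.013 to 0.075. For mothers: median 0.011, interquartile range 0.007 to 0.037.
- **Sample size and power, assumption.** The ICC used is "0.01 for maternal and neonatal outcomes, and no more than 0.1 for hospital staff outcomes". The reason: "As we will collect baseline data, we will be able to gain precision, allowing us to reduce ICC".
- **Sample size and power, formula.** It defines the ICC as unconditional and has separate R-squared terms for variance explained by covariates, between and within clusters. Of these terms it says "when they equal zero the formula reduces to the standard cRCT one, applicable in our case".
- **Table 1 and the text below it.** The mother/child MDE is 0.196 SD at ICC 0.01 and 0.390 SD at ICC 0.1, reported as a range of 0.196 to 0.39.
- **Sample size, sampling, and recruitment.** Every survey round draws a fresh cross-section of 1,250 mothers.
- **Statistical methods.** The model has region fixed effects and hospital controls chosen by machine learning. ANCOVA is for units measured at both rounds, and difference-in-differences is for those without a baseline value.

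**The concern.** Maternal and neonatal outcomes share one ICC. For maternal outcomes 0.01 agrees with the cited median of 0.011. For neonatal outcomes it is less than a fifth of the cited median and below the cited lower quartile, so the whole case for it rests on the baseline data.

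That case is asserted and not quantified. The formula has a place for such a gain, the cluster R-squared, but it is used with that term at zero and the gain is taken by lowering the ICC. The design also limits the gain: no mother has her own baseline value, so the survey can adjust only for the average of other mothers in the same hospital.

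Neonatal health belongs to one of the two primary outcome sets. If a null neonatal result is read against 0.196 SD, effects of 0.2 to 0.3 SD may be taken as ruled out when the trial had limited power to see them.

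**Working it through.** **Inputs.** Significance level and power: "of 0.05 and power" "of 0.8 using two-sided tests". Cluster size: "We aim to interview on average 30 hospital staff per hospital and 50 mother-newborn pairs". So m = 50 mothers per hospital, and 1,250 / 2 = 625 per arm. SD = 1 (outcomes standardised). Both R-squared terms = 0.

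**Step 1. Reproduce Table 1.** MDE = k × sqrt(2 × [m × ICC + (1 − ICC)] / n), where k is the sum of the two critical values.

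- ICC 0.01: bracket = 0.50 + 0.99 = 1.49. With k = 2.84, 2.84 × sqrt(2.98 / 625) = 0.196.
- ICC 0.1: bracket = 5.0 + 0.9 = 5.9. 2.84 × sqrt(11.8 / 625) = 0.390.

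With k of about 2.84 all five cells of Table 1 are matched to within 0.2%. The normal multiplier (2.802) gives 0.1935 for the first cell, and t with 23 df (2.926) gives 0.202. I keep 2.84 for comparability.

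**Step 2. Cited neonatal ICCs, no adjustment.**

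| ICC | bracket | MDE (SD) |
|---|---|---|
| 0.013 (lower quartile) | 0.65 + 0.987 = 1.637 | 0.206 |
| 0.054 (median) | 2.70 + 0.946 = 3.646 | 0.307 |
| 0.075 (upper quartile) | 3.75 + 0.925 = 4.675 | 0.347 |

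Power for 0.196 SD at ICC 0.054: SE = sqrt(2 × 3.646 / 625) = 0.108, so 0.196 / 0.108 − 1.96 = −0.145 and power is about 44% (normal approximation). The same sum at ICC 0.01 gives 81%.

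**Step 3. Cluster R-squared needed.** From 0.054 to 0.01: 1 − 0.01 / 0.054 = 0.81. Two other definitions give nearly the same: 0.80 to bring the formula's MDE to 0.196, and 0.82 for a residual ICC of exactly 0.01.

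**Step 4. What survey hospital means can supply.** The reliability of a 50-mother mean at ICC 0.054 is m × ICC / [m × ICC + 1 − ICC] = 2.7 / 3.646 = 0.74. If c is the correlation of true hospital effects between rounds, cluster R-squared = c² × 0.74. The protocol gives no c, so the values below are assumptions.

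- c = 1: R-squared 0.741. Bracket = 2.7 × 0.259 + 0.946 = 1.646, MDE 0.206.
- c = 0.8: R-squared 0.474. Bracket = 2.7 × 0.526 + 0.946 = 2.366, MDE 0.247.
- c = 0.5: R-squared 0.185. Bracket = 2.7 × 0.815 + 0.946 = 3.146, MDE 0.285.

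These are for ANCOVA on hospital means. For difference-in-differences the bracket is 2 × 3.646 × (1 − 0.74c), which gives 0.221, 0.277 and 0.344 SD for the same three values of c. None reaches 0.196.

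**Step 5. Where the shortfall disappears.** At ICC 0.013 the reliability is 0.65 / 1.637 = 0.397. With c = 0.8 the R-squared is 0.254, the bracket 0.65 × 0.746 + 0.987 = 1.472 and the ANCOVA MDE 0.195. An outcome near the lower quartile can therefore meet the stated figure.

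**The case against.** **The printed range already covers these values.** This stands. Table 1 and the text give 0.39 SD at ICC 0.1, above the 0.347 found at the upper quartile. A reader might infer that the whole range, or the arithmetic of Table 1, is wrong. Neither is so: the table reproduces. But 0.01 is the only ICC the text assumes for newborns, and nothing shows that the cited median gives an MDE well above the lower end.

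**Survey means are not the only hospital information.** This also stands. Region effects and selected hospital controls can explain cluster variance. The section on data collection and management also describes administrative hospital data from before the programme, though it assigns them to the regression discontinuity analysis. A reader might infer that 0.01 is unattainable. The documents do not show that. They show that survey means alone fall short at the cited median, and they give no figure for the rest.

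**Lowering the ICC is close to raising the cluster R-squared.** True: entering both would double count, so zero R-squared with a conditional ICC could be a matter of presentation. What is missing is the R-squared that the reduction implies, and the baseline survey alone does not reach it.

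**The source may not fit.** The cited ICCs come from other countries, while this trial compares high-volume hospitals within three regions of one country. So 0.307 SD is the result at the cited median, not the MDE this trial will have. The protocol offers no other neonatal source.

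**Multiplicity.** The protocol says "We will additionally adjust for multiple hypothesis testing by family of outcome", while the MDEs use 0.05. A reader might add a penalty for this. Neither a family size nor a method is stated, so no figure can be attached, and I make no point of it.

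**Conclusion.** The ICC of 0.01 is not supported for neonatal outcomes, and neither is the 0.196 SD lower bound that follows from it, at the median ICC the protocol cites. Without adjustment the MDE there is 0.307 SD, or 57% above 0.196 (0.307 / 0.196 = 1.57). With ANCOVA on hospital means it is about 0.206 SD if hospital effects are perfectly stable, some 5% above, and 0.247 SD at an assumed between-round correlation of 0.8.

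This rests on 50 mothers per hospital, SD 1, the Table 1 multiplier and the assumed between-round correlations. Hospital samples of 35 to 65 and t-based critical values would raise the MDEs slightly (0.316 SD at ICC 0.054 with 23 df). The point does not touch maternal outcomes, the upper bound or the sample size. It concerns an assumption and how it is reported.

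**What to change.** 1. Split the mother/child row of Table 1. Keep ICC 0.01 for maternal outcomes, in line with the cited median of 0.011.
2. Add a neonatal row without covariates at ICC 0.013, 0.054 and 0.075: 0.21, 0.31 and 0.35 SD. Restate the range in the text separately for the two groups.
3. If a baseline gain is claimed, leave the ICC unconditional and enter the gain as a stated cluster R-squared, with the between-round correlation assumed. The part that comes from survey means should not exceed the reliability of a 50-mother mean. Any further part from region effects or hospital covariates needs its own figure and source.

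The cost is restated figures and a less favourable lower bound for neonatal outcomes. Design, sample size and conduct stay as they are.

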### Methods and trial design

This study uses a cluster randomized controlled trial (cRCT) to evaluate the impacts of the introduction of the OTIP Champions program across high-volume hospitals in the final phase of its nation-wide rollout. The cRCT will be integrated into the final phase of the national rollout of the OTIP training program, covering the Central, Greater Accra and Western regions. 12 of the 25 hospitals are randomly assigned to receive OTIP training in September 2024, and the remaining 13 receive OTIP approximately 4 months later. Figure 1 is the design flow diagram. SPIRIT reporting guideline were used [11].

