#### Study setting

The Government of Ghana, through Ghana Health Services, is rolling out OTIP to all high-volume hospitals (defined as hospitals with more than 1,200 births in 2022) in different regions of the country. In 2023, the average total number of deliveries in these high-density hospitals was 2,146. The average maternal mortality rate was 110 per 100,000 live births, and the average neonatal mortality rate was 8.21 per 1,000 live births. In hospitals across Ghana, the average total number of deliveries in 2023 was lower, at 1,688. The average maternal mortality rate was slightly higher at 126 per 100,000 live births, while the average neonatal mortality rate was slightly lower at 7.7 per 1,000 live births.

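### Table 1's minimum detectable effect cannot apply to maternal and neonatal mortality: at the setting's own rates, 0.196 SD exceeds the whole death rate

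*Protocol article*

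**What the plan says.** Under Sample size and power, the protocol sets a two-sided significance level of 0.05 and power of 0.8, and plans 25 hospitals with on average 50 mother-newborn pairs each, 1,250 per round. For the calculation it states: "we assume that all outcomes considered will be continuous normally distributed variables standardized to have mean zero and standard deviation of one". It concludes that the MDE depends on the sample size of each outcome group and not on the outcome. Table 1 accordingly has one mother/child row, 0.196 SD at an ICC of 0.01 and 0.390 SD at an ICC of 0.1, and the text repeats: "For maternal and newborn outcomes, the MDE is between 0.196 and 0.39".

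The Outcomes section gives maternal and neonatal mortality as examples within the second primary set. Statistical methods applies a regression at the level of the mother or baby to process, maternal and neonatal outcomes alike. On frequency, Study setting says of the high-volume hospitals in 2023: "The average maternal mortality rate was 110 per 100,000 live births", and "the average neonatal mortality rate was 8.21 per 1,000 live births".

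Mortality is also handled elsewhere. Data collection and management takes monthly hospital mortality from the national administrative system, and Methods for additional analyses describes a regression discontinuity design (RDD) with the mortality rate as outcome, intended to complement the cluster trial.

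**The concern.** Death is a binary outcome, and in these hospitals a rare one. The SD of a binary outcome is fixed by its risk, and the largest possible benefit is to bring the risk to zero. An MDE in SD units therefore has to be checked against the base rate. If the MDE is larger than the base rate, no reduction of that size can occur, and the 80% power attached to it has no meaning for that outcome.

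The protocol neither makes this check nor exempts mortality from the mother/child row. Survival is part of the first research question, so a reader who meets a non-significant mortality result from the cluster trial could set it against a published 80% power figure and take it for evidence that the programme does not affect survival.

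**Working it through.** **Inputs.** Two-sided alpha 0.05, power 0.80, 25 hospitals, mean cluster size m = 50 and N = 1,250 (Sample size and power). Allocation of 12 early and 13 late hospitals (Methods and trial design), so about 600 against 650 pairs. ICC 0.01, the protocol's assumption for maternal and neonatal outcomes. Risks of 0.00821 neonatal and 0.00110 maternal (Study setting). As upper sensitivity values, the national rates of 22.8 per 1,000 and 263 per 100,000 (Abstract; Background and rationale).

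**1. The plan's own figure.** MDE = (1.960 + 0.842) × sqrt{[1 + (m − 1) × ICC] × (1/n1 + 1/n2)} with SD = 1.

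| ICC | Design effect | Computed MDE | Table 1 |
|---|---|---|---|
| 0.01 | 1.49 | 0.194 | 0.196 |
| 0.1 | 5.9 | 0.385 | 0.390 |
| 0.3 | 15.7 | 0.628 | 0.637 |

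Table 1 reproduces within 3%. The formula is not at issue; the outcomes to which it is applied are.

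**2. Conversion to the risk scale.** SD = sqrt[p(1 − p)] in the control group, which is the protocol's own standardisation. The MDE in risk units is 0.196 × SD. The largest possible reduction is p, or p/SD in SD units.

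| Outcome | p | SD | 0.196 SD as a risk | Multiple of p | Eliminating all deaths |
|---|---|---|---|---|---|
| Neonatal, setting | 0.00821 | 0.0902 | 17.7 per 1,000 | 2.15 | 0.091 SD |
| Maternal, setting | 0.00110 | 0.0331 | 650 per 100,000 | 5.9 | 0.033 SD |
| Neonatal, national | 0.0228 | 0.149 | 29.3 per 1,000 | 1.28 | 0.153 SD |
| Maternal, national | 0.00263 | 0.0512 | 1,004 per 100,000 | 3.8 | 0.051 SD |

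**3. Where the SD scale breaks down.** A reduction of d SD is possible only if p ≥ d × sqrt[p(1 − p)], that is p ≥ d²/(1 + d²). For d = 0.196 this is 0.0384/1.0384 = 3.7%. For d = 0.390 it is 0.1521/1.1521 = 13.2%.

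**4. Power with the correct binomial variances.** Arm sizes are divided by the design effect of 1.49. For a halving of neonatal mortality at 8.21 per 1,000 with 625 per arm, the difference is 0.0041 and SE = sqrt[1.49 × (0.00814 + 0.00409)/625] = 0.0054. Power is Φ(0.76 − 1.96), about 0.12. The ranges below cover pooled and unpooled variance with 600 against 650.

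| Scenario | Halving | Elimination |
|---|---|---|
| Neonatal, 8.21 per 1,000 | 11–12% | 44–48% |
| Neonatal, 22.8 per 1,000 | 24–25% | 87–89% |
| Maternal, 110 per 100,000 | 4–5% | 9–10% |

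**5. Expected deaths.** Among 650 control deliveries: 650 × 0.00821 = 5.3 neonatal and 650 × 0.00110 = 0.7 maternal. The survey would record fewer. It interviews mothers after delivery, so a maternal death cannot appear in it. Sample size, sampling, and recruitment adds that mothers in distress, for instance after losing a child in labour, are not approached.

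**The case against.** The best defence is that mortality was never meant to rest on the survey. The RDD is introduced as the way to examine mortality, administrative records are a named data source, and the Outcomes section ties no outcome to the interviews. This stands in part: a mortality analysis on administrative counts is already planned, and it would be wrong to infer that the protocol has no other plan for mortality. It does not remove the error. The RDD sits among the additional analyses as a complement, mortality stays in the primary set and under the mother-or-baby regression, and nothing exempts it from Table 1.

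A second defence is that the SD scale is an ordinary planning device and the protocol states its assumption openly. That holds for continuous scores, indices and common binary outcomes: at a control risk of 50%, 0.196 SD is 0.196 × 0.5 = 9.8 percentage points, a usable figure. A reader might infer that Table 1 is void for every binary outcome; step 3 shows that the problem is confined to low risks.

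A third defence is that Table 1 never names mortality and that how a null result would be read is conjecture. The first part is true, but the row covers the whole group to which mortality belongs. The second is a fair caution: misreading is a risk, not a certainty.

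**Conclusion.** The point holds for mortality and should be corrected. At the setting's own rates, the smallest MDE for the mother/child group is 2.15 times the whole neonatal rate and 5.9 times the whole maternal rate, so the stated 80% power does not exist for either outcome. A halving would be detected about 11–12% of the time (neonatal) or 4–5% (maternal).

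A tempting stronger claim is that no protective effect, however large, could be detected. The figures do not support it. The comparison in SD units uses the control-group variance for both arms, whereas the treated-arm variance shrinks as deaths are prevented. Allowing for that, elimination of all neonatal deaths has about 44–48% power at 8.21 per 1,000 and 87–89% at 22.8 per 1,000. Even at the higher rate, a halving has only about 24–25%.

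These figures assume an ICC of 0.01, equal clusters of 50, full capture of deaths and a normal approximation, which is rough with so few events. Incomplete capture would reduce the expected deaths further.

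**What to change.** In Sample size and power, state that Table 1 does not apply to mortality or other rare binary outcomes, and that mortality is not powered in the 1,250-mother survey. In Outcomes, remove mortality from the survey-based primary set of the cluster trial, and say that conclusions on mortality will rest on the administrative-data analysis already described under Data collection and management and Methods for additional analyses. For any other low-risk binary outcome that stays primary, give the MDE in percentage points at the expected control rate; below about 3.7% (or 13.2% at the larger MDE) the SD figure should not be shown. Keep the SD scale for continuous outcomes, indices and commoner binary outcomes.

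The cost is rewording and a less favourable power statement for mortality. No extra participants or data collection are needed.

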#### Eligibility criteria

The cRCT will focus on the 25 hospitals that will receive the OTIP program during the final phase of the national roll-out, which has been planned in three phases (see Supplementary Materials S.3 for names of study sites). The first two phases of the roll-out were completed by April 2024. The third and final phase of the rollout was started in September 2024, covering all eligible hospitals, 25 in total, in Greater Accra, Central and Western regions.

Within each study hospital, target participants will be mothers that delivered in the hospital within the last two months prior to data collection. They will not be selected if they are facing post-birth complications, or if they are below the age of 18 and a guardian is not present. Data from mothers recruited in January 2024 will be the basis for the impact evaluation. We in addition collect information from mothers who were present prior to intervention implementation. These will however not be exposed to the OTIP intervention.

We will further conduct interviews with individuals who will perform the intervention, e.g. midwives. We will interview those that are selected to be OTIP champions, and a random sample of non-champion midwives on permanent contracts in the maternity department, including those in charge of wards and clinics. We will also administer online surveys to all the midwives on permanent contracts working in each hospital to collect data on clinical knowledge (1,338 midwives in total).

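### The minimum detectable effects printed for process outcomes assume 1,250 mothers, but the doctor-intervention outcome is worded to count only mothers with complications, so the printed figures are too favourable for it

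*Protocol article*

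**What the plan says.** Under Outcomes, the article gives four examples of primary process variables. Three apply to any mother or newborn: time to initial assessment, assessment on arrival, and postnatal checks. The fourth is "doctor intervened if complications during labour and delivery at the hospital".

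Under Sample size and power, the planned sample is stated as: "We aim to interview on average 30 hospital staff per hospital and 50 mother-newborn pairs". That makes 1,250 mothers per round. Table 1 then has a single process row, labelled with 1,250, showing MDEs of 0.196, 0.390 and 0.637 SD at ICCs of 0.01, 0.1 and 0.3. The text treats every outcome as continuous with SD 1 and says that the MDEs "do not vary by outcomes, but rather by sample size we have for each outcome group". It concludes: "For process variables, our RCT sample yields MDEs between 0.196 and 0.64 for two-sided tests". No process outcome is excepted, and neither a complication share nor a smaller sample size for any process outcome is given.

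Under Eligibility criteria, a separate rule on selecting mothers reads: "They will not be selected if they are facing post-birth complications".

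**The concern.** On the article's own account, sample size is what separates one MDE from another. The sample size printed for the process group is the number of mothers interviewed. An outcome that asks whether a doctor intervened, given complications, is observed only in the mothers who had them. For that outcome both the number per hospital and the total are smaller than Table 1 assumes.

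What is at stake is how a result on this outcome is read. The Intervention section says that high-risk cases call for a doctor, so this is one of the places where the programme should show an effect. A reader who sees no difference will set it against 80% power at 0.196 to 0.64 SD. If the outcome rests on a fraction of the mothers, that benchmark is too favourable and a null finding carries less information than it appears to.

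**Working it through.** **Inputs from the article.** Two-sided alpha 0.05; power 0.80; SD 1; covariate R-squared terms zero; 50 mothers per hospital on average; 25 hospitals ("12 of the 25 hospitals are randomly assigned" to early training, so 12 against 13). I use 12.5 hospitals per arm, that is n = 625 mothers per arm. Using 12 and 13 instead changes the MDE at ICC 0.01 only from 0.1935 to 0.1936 (normal multiplier).

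**Step 1: reproduce Table 1.** The standard two-arm cluster form is

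MDE = c × sqrt{ 2 × [1 + (m − 1) × ICC] / n }, with m mothers per hospital and n per arm.

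With c = 2.84, m = 50 and n = 625:

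- ICC 0.01: 2.84 × sqrt(2 × 1.49 / 625) = 0.196
- ICC 0.1: 2.84 × sqrt(2 × 5.90 / 625) = 0.390
- ICC 0.3: 2.84 × sqrt(2 × 15.70 / 625) = 0.637

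These are the printed values. The multiplier 2.84 is the one implied by Table 1 and corresponds to a t-distribution on about 70 degrees of freedom. The normal multiplier 2.80 gives 0.194, 0.385 and 0.628, within about 1.5%. Either way, the row is obtained only if all 50 mothers per hospital count.

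**Step 2: restrict to mothers with complications.** Let f be the share of interviewed mothers with complications. The article does not give f, so 10% to 50% is assumed, with the same f in every hospital and the ICC unchanged. Replace m by 50f and n by 625f. For example, at f = 20%, m = 10 and n = 125, and at ICC 0.01 the MDE is 2.84 × sqrt(2 × 1.09 / 125) = 0.375.

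MDE in SD (c = 2.84), with power at the printed MDE in brackets (noncentral t, 70 df):

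| f | Mothers in total | ICC 0.01 (printed 0.196) | ICC 0.1 (printed 0.390) | ICC 0.3 (printed 0.637) |
|---|---|---|---|---|
| 100% | 1,250 | 0.196 (80%) | 0.390 (80%) | 0.637 (80%) |
| 50% | 625 | 0.253 (58%) | 0.419 (74%) | 0.651 (78%) |
| 40% | 500 | 0.277 (51%) | 0.433 (71%) | 0.658 (77%) |
| 30% | 375 | 0.313 (42%) | 0.454 (67%) | 0.669 (76%) |
| 20% | 250 | 0.375 (31%) | 0.495 (60%) | 0.691 (73%) |
| 10% | 125 | 0.518 (18%) | 0.601 (44%) | 0.754 (66%) |

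With the normal multiplier, the 50% row is 0.250, 0.413 and 0.642 (power 60%, 75%, 79%), and the 10% row is 0.511, 0.593 and 0.743 (19%, 45%, 67%). The choice of multiplier does not alter the picture.

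**Step 3: a mid-range ICC.** The article quotes a median ICC of 0.067 for process variables. At that value the full-sample MDE is 2.84 × sqrt(2 × 4.283 / 625) = 0.332. For f = 50%, 40%, 20% and 10% it becomes 0.367, 0.383, 0.455 and 0.572, and power at 0.332 is about 72%, 68%, 53% and 37%.

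**Why the gap narrows as the ICC rises.** At ICC 0.3 most of the variance of a hospital mean comes from differences between hospitals, and losing mothers within hospitals adds little to it.

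**The case against.** The strongest reply is that the outcomes are given as examples in a short parenthesis, not as operational definitions, and that item coding is commonly left to a fuller document. If mothers without complications were coded as no intervention and kept in, the denominator would be 1,250 and the point would fall. It is fair that the analysis population is not spelled out. But nothing in the article supports that coding, and the wording is conditional. Complications are also listed as an outcome in their own right, so coding zeros would mix how often complications occur with how staff respond to them. The range is stated for process variables without exception, and this is one of the four it names.

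A second reply is that Table 1 is an openly simplified table by outcome group and that its arithmetic is right. Both are true. The fault is in applying one sample size to an outcome that does not have it.

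Three stronger readings are tempting and are not supported:

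- A reader might infer that the whole printed range fails, or that the trial cannot detect effects of that size. At ICC 0.1 the recalculated MDEs of about 0.41 to 0.60 still lie between 0.196 and 0.64, although above the tabulated 0.390. At ICC 0.3 power at 0.637 is still about 66-79%.
- A reader might take 18% power as the finding. It pairs the smallest assumed share with the smallest assumed ICC, and the true share is unknown.
- A reader might say that the selection rule "They will not be selected if they are facing post-birth complications" certainly shrinks the group. That rule concerns complications after birth, whereas the outcome concerns labour and delivery, and mothers may be interviewed up to two months later. The groups can overlap, so the subset may be smaller still, but the calculation does not use this.

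**Conclusion.** The point holds for the doctor-intervention outcome as worded. The printed MDEs are too favourable for it at any complication share below 100%; only the size depends on the unstated share. Over an assumed 10% to 50%, and across both multipliers, the MDE is:

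- about 0.52 to 0.25 SD at ICC 0.01, with power at the printed 0.196 of about 18-60%;
- about 0.60 to 0.41 at ICC 0.1, with power at the printed 0.390 of about 44-75%;
- about 0.75 to 0.64 at ICC 0.3, with power at the printed 0.637 of about 66-79%.

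The discrepancy is material at low to moderate ICC and small at the top of the assumed range. The conclusion rests on the conditional reading of the outcome, an assumed complication share that is equal across hospitals, and the article's own ICCs carried over to the subset. It concerns the stated power only. The process outcomes defined for every mother are untouched.

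**What to change.** In Table 1, restrict the process row labelled 1,250, and the sentence that summarises it, to process outcomes defined for every mother. Add a row for the outcome conditional on complications, calculated with the expected number of mothers with complications per hospital. The pre-intervention round of September 2024 could supply that number, since it surveyed mothers in the same hospitals. If the outcome is in fact meant to be defined over all mothers, say so and state how mothers without complications are coded.

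The cost is one table row and one restated sentence. No extra mothers and no change of design are needed. The downside is a less favourable stated MDE for this outcome.
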